## Data management

### Data sources

Obstetric and neonatal outcome data will be obtained from either the onsite obstetric database where available or the Perinatal Data Collection unit in each state.

The VAS will be used to measure perceptions of pain. The VAS is an ungraded 100 mm long horizontal straight line with the endpoints “no pain” to the left (0) and “worst pain imaginable” to the right (100)
[52]. To record a VAS, a participant marks a point on the line that matches the amount of pain experienced. The point is then quantified by measuring the distance in millimetres between “No Pain” and the point marked by the woman against a 0-10 cm gauge. The VAS has been shown to be sensitive to pain intensity and most individuals have no difficulties with its use
[53].

Data for the cost effectiveness analysis (CEA) will be obtained from the perinatal database and will include data on interventions during labour and the postnatal period, length of stay, admission to neonatal nursery, mode of birth, and other analgesia requirements. In addition, data on staffing required during labour (number of midwives and time required from each midwife for care provided during labour) will be collected. Data on hospital costs will be obtained through the health service managers. These will include staffing, equipment and consumables for each woman and baby.

### Data entry and storage

Identified data collection forms will be kept in locked storage on each site prior to secure transfer to the Project Team. Upon receipt, data will be entered onto a specifically designed password protected database by designated research staff, all individual data will be de-identified through allocation of a unique study code. Data entry and storage, both paper and electronic will be managed and maintained as specified in the Human Research Ethics Committee (HREC) approvals for a period of not less than 15 years.

## Data analysis

### Statistical methods

All women who underwent randomisation will be analysed in their allocated treatment groups (ie. intention to treat). Relative risks with 95% confidence intervals for the primary outcome will be calculated. Secondary outcome measures of categorical data will be analysed with chi-squared tests and continuous data will be analysed with t-tests for normally distributed data and Mann–Whitney *U* test for parametric data. Regression will be used if necessary to adjust for any other confounding variables. All study outcomes will be analysed using a two-sided P value of < 0.05 to indicate statistical significance. The study is only powered to report the primary outcome and for secondary outcomes confidence intervals (CI) will be included as a measure of the effect size. Differences in pre and post VAS scores will be reported in the format recommended by the recent Cochrane Review
[54].

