### Lower back pain in labour – a significant problem

One in three women will experience continuous lower back pain in labour
[17]. The occipito-posterior (OP) position of the fetus has been cited as a common contributing factor
[18] although there is a paucity of evidence to support or refute this observation
[19]. The OP position results in deflexion of the fetal head, which then presents a larger diameter as it enters and progresses through the maternal pelvis, hence contributing to obstructed labour and an increased risk of interventions including epidural anaesthesia and caesarean section
[20]. Labour dystocia, characterised by very slow progress in labour together with significant and prolonged pain, further increases the risk of intervention, particularly epidural anaesthetic and CS
[20]. Indeed, labour dystocia has been reported as the major reason for a CS during labour
[21]. However, due to differences in Australian state and territory perinatal reporting, no data are available on the actual number performed for this reason. That said, a major Australian metropolitan hospital reported labour dystocia as the primary indication for 12.4% of all CSs performed in 2007
[22], with other research suggesting it was more common in women having their first baby (primiparous), accounting for nearly 80% of CSs performed during labour
[23].

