### Sample size

The meta-analysis of SWI use reported the overall rate of ‘in labour’ CS as 9.9% in the control group and 4.6% in the intervention (SWI) group
[36] – i.e. a greater than 50% reduction in the CS rate in the SWI group. However, the review included trials where women receiving SWI were compared with women receiving either a placebo or other interventions (eg. acupuncture), and included trials that were conducted over two decades ago (1990 to 2008): a significant increase in CS rates (% in 1991
[49] to 31.5% in 2009
[50]) has been recorded in the intervening period.

More recently, at a metropolitan hospital in QLD, routine birth outcome data were collected on all women in labour who received SWI during 2010 (n = 427). The CS rate for women in the SWI group was 12.5%. The ‘in labour’ CS rate for women receiving standard care during the same period was 17.5%. This represents a difference of 30% which we suggest may conservatively reflect the contemporary clinical trend in CS rates. To demonstrate a similar reduction (17.5% to 12.5%), our study requires 839 women in each group (80% power, type I error 0.05). The attrition rate in our previous trial was 13%
[48], however this was largely due to women giving birth prior to the measurement of the primary outcome (pain at 30 mins) and the use of nitrous oxide inhalation prior to randomisation. Neither of these are exclusion factors in this trial, therefore we expect attrition to be minimal and propose an attrition rate of 10%. The total sample size required is therefore 1886 women. As some sites have higher annual birth rates than other sites, the recruitment allocation anticipated for each site will be proportional.

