### Randomisation and blinding

Blinded (plain label) ampoules of sterile water (intervention) and normal saline (placebo) for injection will be prepared by the Mater Health Service Pharmacy for all sites, and labelled according to a randomisation schedule prepared by the Mater Medical Research Institute. The ampoules will be delivered to each of the sites and stored in a locked container. The randomisation schedule will use permuted blocks and will be stratified by research site. In our previous trial about 10% of participants requested a repeat dose, to provide for this with minimal crossover between groups (e.g., women randomised to normal saline receiving sterile water as a repeat dose) each allocation packet will include two ampoules of the allocated treatment. Following consent, two midwives (other than the midwife assigned to provide the woman’s care in labour, or ‘primary midwife’) will obtain the next ampoule in numbered order and administer the injections. As this is a double blind trial, the administering midwives will be unaware of the arm to which the participant has been allocated. The ampoule number will be recorded in a research log and on the data collection forms. As the injection of normal saline does not result in the same degree of administration pain as sterile water, both interventions will be administered by midwives other than the primary midwife, who will be absent from the room throughout. This will prevent the primary midwife from observing the woman’s reaction to the administration which reduces the likelihood of assumptions being made about the arm of the trial into which the woman has been randomised.

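### The primary relative risk is not tied to the site stratification, and an open-ended rule for regression leaves unsettled whether a crude or an adjusted estimate decides the trial

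*Protocol article*

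**What the plan says.** On allocation, Randomisation and blinding states: "The randomisation schedule will use permuted blocks and will be stratified by research site". Site is the only stratification factor given.

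On the primary outcome, caesarean section (CS) in labour, Statistical methods states: "Relative risks with 95% confidence intervals for the primary outcome will be calculated". Neither site nor any covariate is mentioned. After a sentence on tests for secondary outcomes, the same section continues: "Regression will be used if necessary to adjust for any other confounding variables". The next sentence sets the significance level: "All study outcomes will be analysed using a two-sided P value of < 0.05 to indicate statistical significance".

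Parity is not a stratification factor and is not named in the analysis. The Background does treat first births as different. It describes labour dystocia as "more common in women having their first baby (primiparous), accounting for nearly 80% of CSs performed during labour", and elsewhere it links epidural use with CS particularly in nulliparous women.

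**The concern.** The regression sentence is a rule, but three things in it are badly fixed.

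- **Trigger.** *If necessary* has no criterion, so the decision can be taken after seeing the baseline table or the crude result.
- **Variables.** *Any other* confounders has no antecedent, because no variable is named before it. The article itself supplies several candidates: site, parity, induced or spontaneous labour, and the vaginal assessment and fetal position before randomisation.
- **Rationale.** In a randomised trial, baseline differences arise by chance. The sound reason to adjust is that a factor is prognostic, and that can be decided beforehand.

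The factor that structured the randomisation is also not carried into the stated primary analysis. At stake are a little precision and, more importantly, clarity about which number is the result of the trial's only powered comparison.

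**Working it through.** **Inputs from the article.** Control rate: "The ‘in labour’ CS rate for women receiving standard care during the same period was 17.5" per cent. Intervention rate: "The CS rate for women in the SWI group was 12.5" per cent. Size: "our study requires 839 women in each group (80% power, type I error 0.05"). The test is two-sided and six hospitals have confirmed involvement. The article gives no CS rate by parity, no nulliparous share and no site-specific rates, so these are assumed below.

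**1. The plan's own figure.** With pooled rate 0.15 and difference 0.05:

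n' = [1.960·√(2·0.15·0.85) + 0.8416·√(0.175·0.825 + 0.125·0.875)]² / 0.05² = (0.9897 + 0.4240)² / 0.0025 ≈ 799.4, or 800 rounded up.

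With continuity correction, n = (n'/4)·[1 + √(1 + 4/(n'·0.05))]² = 199.85 × 2.0488² ≈ 838.9, or 839. The stated figure is reproduced exactly. It is a crude two-proportion calculation and takes no credit for adjustment.

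**2. Power of the crude test at 839 per group** (no continuity correction): z = (0.05·√839 − 0.9897)/0.5037 = 0.910, so power is 81.9%. With the correction it is 80% by construction.

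**3. Power if stratified.** For strata with share w, control rate c, treated rate t = c × 0.125/0.175 and mean rate m = (c + t)/2:

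power = Φ{[Σ839w(c − t)/2 − 1.96·√(Σ839w·m(1 − m)/2)] / √(Σ839w[c(1 − c) + t(1 − t)]/4)}

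- *Site*, six equal sites with control rates spread 17.5% ± 0, 3, 5 or 8 points: 81.9%, 82.0%, 82.1%, 82.5%. The gain is 0 to 0.7 points.
- *Parity*, nulliparous share 50 to 80% and nulliparous-to-parous rate ratio 2 to 10: from 82.2% (80%, ratio 2) to 86.4% (50%, ratio 10). The gain is 0.3 to 4.6 points.
- *Worked case* (50%, ratio 10; control rates 31.8% and 3.2%): (20.975 − 1.96 × 6.868)/6.836 = 1.099, so power is 86.4%.

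**4. Chance imbalance in parity.** The 95% range of the difference in nulliparous share is ±1.96·√(2f(1 − f)/839), where f is that share.

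- f = 0.7, rates 22% v 7%: 4.4 points × 0.15 ≈ 0.7 points of CS rate.
- f = 0.6, rates 27% v 3.25%: 4.7 points × 0.2375 ≈ 1.1 points.

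The design target is 5 points. This is sampling variation that the crude interval already covers, not bias.

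**5. Type I error** (6,000 simulated trials, 1,680 women, blocks of four within six equal sites, no treatment effect). The assumptions were 70% nulliparous, rate ratio 4 and sites ± 3 points. Two further factors were assumed: induction (35% of women, relative risk 1.5) and fetal position (30%, relative risk 1.8).

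- Any one analysis fixed in advance: 4.8 to 5.1%. Crude and site-stratified are both 4.9%.
- Most favourable of four (crude, site, parity, site by parity): 6.0%.
- Most favourable of seven (adding three sets that combine parity with induction, position or both): 6.9%.
- With no parity effect and sites ± 8 points, the last two figures fall to 5.3% and 6.2%.

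The simulation standard error is √(0.06 × 0.94/6000) ≈ 0.3 points.

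**The case against.** A fair opponent would make four points.

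- **This is a condensed article.** Covariates and models usually sit in the statistical analysis plan, which is not shown and may settle them. The article is silent on site; it does not exclude it. This stands: silence on site or parity alone would be weak grounds. The regression sentence, however, is not silence. It states a conditional rule, which an analysis plan would have to override.
- **The sentence may govern only secondary outcomes,** since it follows the tests for those. That reading is possible. Nothing in the text limits it that way, and the next sentence covers all outcomes.
- **Site hardly matters.** Care during labour says that intervention rates, CS included, are similar across sites. This stands, and it puts the gain from site near zero.
- **Parity was not a stratification factor.** This stands: leaving it out breaks no design feature, and every figure for its benefit is assumed.

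A reader might infer from the Background that first births account for nearly 80% of caesareans in labour, and so that the gain from parity is large. The phrase most naturally means dystocia's share of in-labour caesareans among first births. It supports parity as prognostic but gives no rate by parity.

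**Conclusion.** The point holds as a low-cost improvement to a badly fixed rule. The stated analysis does not carry site into the primary relative risk, and it does not settle whether a crude or an adjusted estimate decides the trial.

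Two stronger readings are tempting and are not supported. One is that the trial is underpowered as analysed. The 839 per group was calculated for a crude comparison, which keeps about 82% power, so only a possible gain is lost: under 1 point for site and about 0.3 to 4.6 for parity under the assumed rates. The other is that the plan inflates the type I error to 6 or 7%. Ignoring site leaves it at about 4.9%. The higher figures describe picking the most favourable of several analyses, which the article nowhere says will be done. Adjustment triggered by observed imbalance was not simulated. The 6 to 7% therefore marks what the wording leaves room for, in an illustrative worst case; it is not an expected error rate.

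**What to change.** Replace the regression sentence with one that names a single primary estimator. For example: the primary estimate is the relative risk of CS in labour, by Mantel-Haenszel stratified by site and parity (nulliparous or parous), or by a modified Poisson model with the same terms. Delete *if necessary*, and label the crude relative risk and any other adjustment as supportive. Parity enters as a prognostic factor chosen beforehand, not as a remedy for imbalance.

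If an analysis plan already names the model, it is enough for this section to agree with it. Either way, the choice should be fixed before any comparison by group is seen, including the interim look at 50% enrolment.

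The cost is one sentence. Parity is routine obstetric data and the sample size is unchanged. The only drawback is possibly sparse strata at small sites, which Mantel-Haenszel handles.

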#### Inclusion criteria

Women who:

•In labour (spontaneous or induced, but not dependent on degree of cervical dilation)

•Are ≥ (equal to or greater than) 18 years of age

•Have a term singleton pregnancy (between 37 + 0 and 41 + 6 weeks gestation)

•Have a fetus in a cephalic (head down) presentation

•Experience back pain assessed by visual analogue scale VAS as ≥ 7 when women request analgesia for back pain

•Are able to provide informed consent.

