### Secondary outcomes

•Proportion of women undergoing induction and/or augmentation of labour

•Proportion of women receiving epidural anaesthesia

•Proportion of women having instrumental vaginal births

•Primary indication for CS

•Visual analogue scale of back pain prior to SWI

•Visual analogue scale of back pain following SWI (10, 45 minutes)

•Length of 1st stage and 2nd stage of labour

•Results of most recent vaginal assessment prior to randomisation

•Position of fetal occiput in relation to the maternal pelvis prior to randomisation and how this was determined

•Proportion of women breastfeeding at discharge

•Proportion of neonates admitted to the neonatal intensive care unit

•Cost of care from admission in labour until discharge of mother and baby from hospital from the perspective of the health system.

•Experience of satisfaction, relaxation, social support, negative side effects and memory of pain.

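### Pain scores are compared with unadjusted two-sample tests and pre/post differences although baseline VAS and site are available as covariates, and the Mann-Whitney test is assigned to the wrong kind of data (minor)

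*Protocol article*

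**What the plan says.** All of the following is in the protocol article.

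- **Statistical methods**, tests: "continuous data will be analysed with t-tests for normally distributed data", followed by the Mann-Whitney U "test for parametric data".
- **Statistical methods**, adjustment: "Regression will be used if necessary to adjust for any other confounding variables". No covariate is named.
- **Statistical methods**, pain: "Differences in pre and post VAS scores will be reported in the format recommended by the recent Cochrane Review". The format itself is not reproduced. The section also promises confidence intervals for secondary outcomes and says that only the primary outcome is powered.
- **Secondary outcomes**: the list has both "Visual analogue scale of back pain prior to SWI" and "Visual analogue scale of back pain following SWI (10, 45 minutes"). Epidural use is listed as a separate outcome.
- **Inclusion criteria**: "Experience back pain assessed by visual analogue scale VAS as ≥ 7 when women request analgesia for back pain".
- **Randomisation and blinding**: permuted blocks, stratified by research site.
- **Care during labour**: all women keep access to the usual analgesia, epidural included.

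**The concern.** Relief of back pain heads the list of secondary aims, and the Discussion promises high-level evidence on it. The baseline reading is collected in any case and site is a stratification factor, so a pre-specified adjusted comparison costs nothing. The text instead fixes unadjusted tests and leaves regression to be used if it seems needed, which does not settle the covariates in advance.

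The Mann-Whitney wording is simply wrong. The sentence already gives the t-test to normally distributed data, so the other test must be meant for data that are not. The rule covers every continuous secondary outcome, including length of labour.

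The secondary matter is the 45-minute score. A woman who has had an epidural by then may score low because of the epidural. If that happens more often on placebo, a real benefit of sterile water would look smaller. The protocol's own review of earlier trials faults two of them for not reporting additional pain relief after the injections.

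**Working it through.** **No figure to reproduce.** The plan gives no SD, correlation or target difference for VAS. Its 839 women per group is for caesarean section and does not bear on pain. The pain inputs below are therefore assumptions, except the baseline range of 7-10, which follows from entry at VAS 7 or more on a 0-10 cm gauge.

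**1. Precision formulas.** Let k be baseline SD divided by post-injection SD, and r the correlation of baseline and post-injection VAS. Relative to post-injection scores alone (1), the variance of the between-arm contrast is:

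- change score: 1 + k² − 2rk
- ANCOVA: 1 − r²

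The cost in numbers against ANCOVA is (1 + k² − 2rk)/(1 − r²) for change scores and 1/(1 − r²) for post scores.

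**2. Direct check.** A uniform spread over 7-10 has SD 3/√12 ≈ 0.87.

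- Post SD 2.5 (assumed), k = 0.35:
  - r = 0.2: (1 + 0.1225 − 0.14)/0.96 = 1.02
  - r = 0.4: (1 + 0.1225 − 0.28)/0.84 = 1.00
- Post SD 2 (assumed), k ≈ 0.43:
  - r = 0.2: 1.06
  - r = 0.4: 1.00

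**3. Simulation.** Baseline was drawn from a normal distribution and kept only if within 7-10. Post SD was 2.5 before selection.

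| Latent mean, SD | r before selection | Baseline SD kept | r kept | Change / ANCOVA | Post / ANCOVA |
|---|---|---|---|---|---|
| 7, 2 | 0.3 | 0.81 | 0.13 | 1.04 | 1.02 |
| 7, 2 | 0.5 | 0.81 | 0.23 | 1.02 | 1.05 |
| 7, 2 | 0.7 | 0.81 | 0.37 | 1.00 | 1.16 |
| 8, 1.5 | 0.3 | 0.80 | 0.16 | 1.03 | 1.03 |
| 8, 1.5 | 0.5 | 0.80 | 0.30 | 1.00 | 1.10 |
| 8, 1.5 | 0.7 | 0.80 | 0.46 | 1.01 | 1.27 |
| 6, 2 | 0.3 | 0.78 | 0.12 | 1.04 | 1.01 |
| 6, 2 | 0.5 | 0.78 | 0.22 | 1.02 | 1.05 |
| 6, 2 | 0.7 | 0.78 | 0.36 | 1.00 | 1.15 |

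Together, steps 2 and 3 put the cost at 0-6% in numbers for change scores and 1-27% for post scores alone.

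**4. Epidural before 45 minutes (illustration, all values assumed).** Mean VAS without epidural is 4 on sterile water and 6 on placebo. After epidural the recorded VAS is 1. For comparison, the same women are scored 8.

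With epidural in 5% (sterile water) and 15% (placebo), as observed: (0.85×6 + 0.15×1) − (0.95×4 + 0.05×1) = 5.25 − 3.85 = 1.4. Scored 8: (0.85×6 + 0.15×8) − (0.95×4 + 0.05×8) = 6.3 − 4.2 = 2.1.

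| Epidural, sterile water vs placebo | Difference as observed | Difference if scored 8 |
|---|---|---|
| 5% vs 15% | 1.4 | 2.1 |
| 10% vs 20% | 1.3 | 2.0 |
| 10% vs 30% | 0.8 | 2.2 |
| 5% vs 5% | 1.9 | 1.9 |

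The handling matters only when use differs between arms.

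**The case against.** The strongest reply is that little is lost. The contrast between randomised arms is unbiased with or without adjustment, regression is not ruled out, and the outcome is secondary and unpowered. The cited sentence on VAS concerns a reporting format that the document does not show, and handling of rescue analgesia is commonly left to an analysis plan, which is not available here. All of this stands, and it is why the point is minor. It does not excuse the Mann-Whitney wording, which is an error in the text itself.

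Four stronger readings are tempting, and the documents support none of them.

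- **Change scores waste 30-40% of the women.** The textbook ratio 2(1 − r)/(1 − r²) gives 1.67 at r = 0.2 and 1.43 at r = 0.4, which would mean that. But it assumes equal SDs before and after. The entry criterion that makes r low also shrinks the baseline SD, and the ratio then falls to 1.00-1.06.
- **Regression to the mean distorts the result.** Selection on high pain inflates the fall within each arm, but equally in expectation, so it cancels between arms.
- **Women given an epidural would count as relieved.** The article defines no responder category and states no rule for a score taken after other analgesia. This would be turning silence into a rule.
- **About 13% of pain readings will be lost to births.** The Sample size section says of the previous trial's attrition that "this was largely due to women giving birth prior to the measurement of the primary outcome (pain at 30 mins"), but goes on to name nitrous oxide use before randomisation as a second cause, and gives no split.

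**Conclusion.** The point holds as a minor one. The plan fixes an unadjusted pain analysis where a pre-specified adjusted one is free, and it misstates when the Mann-Whitney test applies.

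The precision gain is modest. It depends on whether the t-test is meant for change or post-injection scores, which the text does not settle, and the ranges rest on assumed post-injection SDs of 2 to 2.5 and correlations of about 0.1 to 0.5 after selection.

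Dilution by epidural is a conditional risk, mainly at 45 minutes. It requires that scores be used as observed and that epidural before the reading be more frequent on placebo. Its size is unknown, since the article gives no epidural rates or timings by arm. The primary outcome, caesarean section, is unaffected.

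**What to change.** 1. State that post-injection VAS at 10 and at 45 minutes will be compared by ANCOVA with baseline VAS and site as covariates, and reported as a between-arm difference with 95% CI. The cited review's format can be kept alongside as a descriptive presentation.
2. Replace *parametric data* with *non-normally distributed data* in the Mann-Whitney sentence.
3. Add a sensitivity analysis in which a VAS taken after epidural or other rescue analgesia is treated as non-response. This needs the time of first rescue analgesia. Data sources mentions other analgesia requirements from the perinatal database, for costing, without saying that times are captured.

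The first two changes cost wording only. The third costs one field on the data collection form, if the time is not already recorded, and it has to be collected prospectively. No sample size changes.
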